## Statistical analyses

### Primary and secondary outcome measures

The primary study outcome, difference in levels of MVPA at 12 weeks between the two treatment groups, will be tested on an intention-to-treat approach, with all participants analyzed in the group to which they were randomized, using a two-tailed 0.05 significance level. We will further conduct per-protocol analysis to evaluate the effect on levels of MVPA at 12 weeks among those who followed the study protocols. Both intention-to-treat and per protocol analyses will be performed on differences in the main and secondary outcomes between the two groups at 12-week and 12-month follow-ups. Mixed-effects regression models will be used for analyses accounting for baseline levels of MVPA and possible clustering of the randomized groups. Similar regression models will be fitted for secondary outcomes. Data will be presented as interclass correlation coefficients, adjusted mean differences (95% confidence interval) and corresponding *p* values. For the primary outcome, within- and between-group changes will also be calculated from a repeated-measures mixed-effects model.

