The intervention entails three face-to-face consultations, in groups of approximately 20 participants, held at the healthcare center. The first consultation, held at the start of the intervention (baseline), will focus on information on how to use the apps and improving motivation to increase walking and exercise, with additional discussions on goal setting and other techniques to support behavior change. The second PA consultation, held at week 6, will focus on semi-structured face-to-face interviews concentrating on facilitating and hindering factors associated with intervention adherence. Participants will review their progress towards achieving the goals set in the first meeting by discussing the information recorded on the walking app and the activity tracker. The final meeting at week 12 will focus on encouraging participants to maintain changes by reviewing goal attainment and discussing relapse prevention strategies to maintain healthy PA and other health habits. After 12 weeks, a purposive sample of participants are interviewed about their experiences of efficacy, implementation and outcomes of the app support and at 12 months with a focus on persistent changes of lifestyle.

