### Sample size calculation

Prior to this study, there were no objectively measured PA data from PA and exercise interventions for young adults with MD. A recent cross-sectional study with objectively measured MVPA showed an average of 11.6 min of MVPA per day (standard deviation 25.1) among individuals with MD [26]. A target between group difference of 10 min of daily MVPA, which has been shown to be a clinically relevant increase in activity, was used for the sample size calculation. For 80% power at the 5% significance level, 40 participants per group is required. To allow for a dropout rate of 20%, approximately 50 participants in each group will be required. Therefore, adopting a conservative approach, the final target sample size will be 55 participants in each treatment arm.

For the qualitative parts of this study, an estimated purposive sample is recruited. Participants are recruited until saturation of data is obtained.

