### Randomization

A block randomization procedure will be used at an individual level to ensure an equal distribution of participants between the two treatment groups. Participants will be randomized before the first baseline assessment at the healthcare center. The SAS Proc Plan (SAS Institute Inc., Cary, NC, USA) will be used for the randomization process. The block size will not be stated in the protocol so that the investigators are blind to the block size. Thus, limiting potential risk for selection bias.

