### Baseline assessment

Participants will be invited to group consultation meetings, including baseline assessments, at a healthcare center. The group consultations will be held at three time points and include all participants recruited from the different recruitment sources.

After a short introduction, participants will perform a battery of physical tests and fill in web-based questionnaires lasting, altogether, approximately 2 h. Thereafter, participants will be randomized into the two treatment groups, followed by separate introductions for their treatment. In addition to the questionnaires described below, the participants will fill in questions on basic demographic information. The baseline measures and all follow-up measures will be made in the morning (fasted state) in order to best utilize standardize measures (e.g. blood samples).

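### The primary model's clustering term names the randomized groups, which are the two arms, and not the groups in which treatment is delivered

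*Protocol article*

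**What the plan says.** The analysis section (Statistical analyses, Primary and secondary outcome measures) states: "Mixed-effects regression models will be used for analyses accounting for baseline levels of MVPA and possible clustering of the randomized groups". It tests the 12-week difference "using a two-tailed 0.05 significance level" and promises to report correlation coefficients alongside adjusted mean differences. It names no other clustering unit.

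Under Randomization: "A block randomization procedure will be used at an individual level". Baseline assessment confirms that participants are allocated to one of two treatment groups.

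On delivery, the Design text for the eHealth program says: "The intervention entails three face-to-face consultations, in groups of approximately 20 participants, held at the healthcare center". The Design text for the supervised program describes weekly sessions with personal trainers, 12 in all. It does not give the number of trainers, the participants per trainer or the session size. Baseline assessment adds: "The group consultations will be held at three time points and include all participants recruited from the different recruitment sources".

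Under Sample size calculation: "For 80% power at the 5% significance level, 40 participants per group is required". The inputs are a 10-minute difference, an SD of 25.1 and 20% dropout. No ICC, cluster size or design effect appears. The final step to 55 per arm is called conservative and is not linked to clustering.

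**The concern.** The sentence on the primary model states which dependence will be modelled, and the unit it names does not work. In an individually randomized two-arm trial, the only randomized groups are the arms. Two arms give one contrast, and the fixed treatment effect already uses it. Nothing is left from which to estimate a between-arm variance, and the promised correlation coefficient has no defined unit.

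The design does create correlation within arms. The eHealth consultations cover motivation, goal setting, progress review and relapse prevention, all meant to influence the primary outcome, and people attend them together. In the supervised arm, participants may share a trainer. If this correlation is missed, the standard error of the treatment effect is too small and the test rejects too often. If it is modelled properly, the trial has less power than a calculation for independent observations suggests.

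**Working it through.** **1. What the named unit can estimate.** Two arm means, less an intercept and a fixed treatment effect, leave 2 − 2 = 0 degrees of freedom for an arm variance. The term is not identifiable.

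**2. The plan's own sample size.** With a difference of 10, SD 25.1, two-sided 5% and 80% power:

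n = 2 × (25.1 × (1.960 + 0.842) / 10)² = 98.9, so 99 per arm.

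The stated 40 is not reproduced. That is a separate fault and not part of this point. To isolate clustering, I take an SD that does justify 40:

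2 × (15.8 × 2.802 / 10)² = 39.2, so 40 per arm.

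**3. Delivery groups in the eHealth arm.** 55/20 = 2.75, so about three groups. After 20% dropout, 55 × 0.8 = 44 are evaluable per arm, and 44/3 = 14.7, so about m = 15 evaluable per group. Three is derived here; the protocol does not state it.

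**4. Variance inflation.** DE = 1 + (m − 1) × ICC. If only the eHealth arm is clustered, the variance of the difference is multiplied by VF = (1 + DE)/2. The documents give no ICC; 0.01 and 0.05 are assumptions.

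| ICC | DE (m = 15) | VF, eHealth arm only |
|---|---|---|
| 0.01 | 1 + 14 × 0.01 = 1.14 | 1.07 |
| 0.05 | 1 + 14 × 0.05 = 1.70 | 1.35 |

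**5. Type I error if the grouping is ignored.** Approximately 2 × [1 − Φ(1.96/√VF)]:

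- ICC 0.01: 1.96/√1.07 = 1.895, giving 5.8%.
- ICC 0.05: 1.96/√1.35 = 1.687, giving 9.2%.

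Simulated t tests with groups of 15, 15 and 14 gave 5.8% to 6.0% and 9.0% to 9.1%, so about 6% and 9%.

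**6. Power at 44 evaluable per arm, SD 15.8.** SE = 15.8 × √(2/44) × √VF, and power = Φ(10/SE − 1.96).

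| ICC | SE | Power, eHealth arm only |
|---|---|---|
| 0 | 3.369 | 84% |
| 0.01 | 3.369 × √1.07 = 3.484 | 82% |
| 0.05 | 3.369 × √1.35 = 3.914 | 72% |

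This is a normal approximation that treats the ICC as known. With about three groups it is poorly estimated, so a test with small-sample degrees of freedom would have somewhat less power.

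**7. What the existing margin covers.** The step from 50 to 55 enrolled leaves 44/40 = 1.10 times the required number. With m = 15, VF = 1 + 7 × ICC, so VF = 1.10 at ICC ≈ 0.014. The margin covers a small ICC in the eHealth arm and no more.

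**The case against.** The strongest reply is that the phrase is loose, not wrong. An ICC for two arms would be meaningless, so the authors probably meant correlation among participants within the groups where they are treated. The plan intends to model clustering, and a condensed article may leave the random-effects structure and the degrees-of-freedom method to a fuller document. Part of this stands. The lack of detail is not a fault in itself, and the type I figures apply only if delivery grouping is ignored or placed on the wrong unit. But the sentence does name a unit, and that unit fails. On the looser reading no unit is named, so the sentence needs correcting either way.

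A second reply is that contact in the eHealth groups is thin: three meetings in 12 weeks, in a program delivered by app. That also stands. It favours the low end of the ICC range, where power stays above 80% on the stated base of 40.

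A reader might infer three stronger claims that the documents do not support:

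- **Groups of about 20 in both arms.** Applying the eHealth structure to both arms gives type I error of about 6.6% and 13%, and power of about 79% and 62%, at ICC 0.01 and 0.05. Groups of that size are described only for the eHealth arm, so these figures are an upper scenario.
- **The trial will exceed its 5% level.** The plan says clustering will be accounted for. The inflation depends on how that is done.
- **The three baseline meetings are clusters that need separate randomization lists.** They include all participants before the arms separate. If both arms are present at each, meeting date is crossed with arm, and ignoring it does not inflate type I error. Separate lists would be a design preference.

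**Conclusion.** The point holds in a limited form. As written, the clustering unit of the primary model is the arm, which is confounded with treatment, and the sample size makes no allowance for the clustering that the analysis anticipates. With the eHealth arm alone clustered in about three groups of about 15 evaluable participants, missing that structure gives type I error of about 6% at ICC 0.01 and 9% at ICC 0.05. Power at 44 per arm, with an SD of 15.8, falls from 84% to about 82% or 72%.

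The wording defect needs no assumption. The sizes rest on assumed ICCs, on a group count derived from 55/20, and on an SD chosen to make 40 per arm correct. The supervised arm may add to them, but the protocol gives nothing from which to say by how much. The correction is worth making and cheap, and the likely effect is modest unless the ICC is well above 0.01.

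**What to change.** Replace the clustering phrase with the delivery unit in each arm, for example: *The model will include a random effect for consultation group in the eHealth arm and for personal trainer in the supervised arm (partially nested, with a separate variance in each arm), with Kenward-Roger or Satterthwaite degrees of freedom. The intraclass correlation will be reported for each arm.*

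Record each participant's consultation group and trainer during delivery. The article gives the trial status as recruiting, and these identifiers are hard to recover later.

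Restate power over a stated ICC range, with the assumed group size, the number of groups in the eHealth arm and the expected caseload per trainer.

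The cost is a change of wording and two extra data fields. Confidence intervals will be wider and stated power somewhat lower, because about three groups estimate an ICC poorly.

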### Health economic evaluation

The cost-effectiveness analyses will be presented as additional cost per additional benefit, that is, additional SEK per health benefit gained, referred to as the incremental cost-effectiveness ratio (ICER). Health benefits include both primary (MVPA) and secondary outcomes and will also be evaluated as moving one individual from an inactive to an active category. Analyses will further account for the costs associated with the eHealth program and standard care supervised health program. Finally, data on HRQoL will be used to assess differences in quality-adjusted life years (QALYs) between the two intervention programs.

### Qualitative analysis

The qualitative data collection and analysis will have a grounded theory (GT) approach [42]. Transcribed data is analyzed according to the steps of GT focusing on the efficacy, implementation and outcomes of the programs and participants’ experiences of persistent lifestyle changes. Also, situational analysis (SA) may be applied; a method evolving from traditional GT. This analysis mainly follows the steps of GT, but SA allows the researcher to identify variations between the discourses and illustrate the socially and time-bound constructions that these discourses are used within. By using SA, three approaches (situational, social world/arena and positional maps) may be applied separately or together so as to communicate the variations in discourses.

## Discussion

The overall aim of the current intervention is to examine the efficacy of an eHealth program compared to a standard care supervised health program to support adults with MD to increase levels of PA and improve health-related behaviors.

### Significance

There is a lack of RCTs investigating effective ways to increase levels of PA in young adults with MD. Increased levels of PA among this physically inactive population have the potential to substantially improve health-related outcomes, possibly more so than in the general population [9]. The few existing studies suggest that motivation for PA and sports participation is high among individuals with MD and that barriers to PA engagement include accessibility to tailored PA, and most importantly, a lack of knowledge on how to engage in PA [6, 11, 12]. The current project aims to fill this gap in knowledge by examining effective and feasible methods to adopt a healthy and active lifestyle for young adults with MD by combining quantitative and qualitative methods. App-based programs are low-cost compared to physical trainers/health coaches. Also, app-based programs can reach most people, as most people in Sweden have smartphones with app-based abilities, while many people may lack money and/or access to physical trainers/health coaches. If a low-cost app-based program can effectively increase short- and long-term levels of PA, then large-scale implementation using apps within rehabilitation and medical centers, as well as workplace settings, is possible within a few years; thus, fundamentally changing general PA counseling approaches for individuals with MD. Further, if this intervention is found to be effective, there are great possibilities to implement the eHealth program to many other groups of inactive people within the population.

## Trial status

Requiting participants.

## Abbreviations

BMI: Body Mass Index
EPN: Regional Ethics Committee
GT: Grounded theory
HRQoL: Health-related quality of life
MD: Mobility disability
MVPA: Moderate to vigorous physical activity
PA: Physical activity
